# The effect of Bushen Culuan Decoction on anovulatory infertile women among 6 different diseases: a study protocol for a randomized, double-blinded, positively controlled, adaptive multicenter clinical trial

**DOI:** 10.1186/s13063-022-06289-7

**Published:** 2022-07-08

**Keywords:** Anovulatory infertility, Basket design, Randomized controlled trial

## Abstract

**Background:**

Anovulation is one of the main causes of female infertility. This study will evaluate the effectiveness and safety of Bushen Culuan Decoction for anovulatory infertility caused by six diseases, including anovulatory abnormal uterine bleeding, polycystic ovarian syndrome, hyperprolactinemia, luteinized unruptured follicle syndrome, corpus luteum insufficiency, and premature ovarian insufficiency.

**Methods:**

This is a randomized, double-blinded, double-dummy, parallel, positively controlled, adaptive, multicenter clinical trial. All participants will be randomly allocated by a central randomization system to the treatment group or the control group in a 1:1 ratio. The treatment group will undergo a 14-day treatment with Bushen Culuan Decoction 13 g three times a day and a 5-day treatment with clomiphene citrate placebo tablets 50 mg once a day starting on day 5 of every menstrual period. The control group will undergo a 14-day treatment with Bushen Culuan Decoction placebo 13 g three times a day and a 5-day treatment with clomiphene citrate tablets 50 mg once a day from day 5 in every menstrual period. The whole treatment will last through 3 menstrual periods or 6 menstrual periods, depending on whether ovulation is regained in the first 3 menstrual periods. All statistical analyses will be performed in SPSS 21.0 (SPSS, Chicago, Illinois, USA), and a *p* value < 0.05 will be considered statistically significant.

**Discussion:**

The objective of this RCT is to evaluate whether Bushen Culuan Decoction enables a higher pregnancy rate than clomiphene citrate in women with anovulatory infertility and to identify the anovulatory diseases for which Bushen Culuan Decoction has higher effectiveness .This study has been approved by the Medical Ethics Committee of Xiyuan Hospital China Academy of Chinese Medical Sciences (No. 2017XLA037-2). The results of this study will be offered for publication in peer-reviewed journals.

**Trial registration:**

ClinicalTrials.gov NCT03709849. Registered on 19 November 2018.

## Background

Anovulation is one of the main causes of female infertility, contributing to 25–30% of all female infertility [1]. The function of the hypothalamic-pituitary-ovarian axis (HPOA) can be disturbed by psychentonia, over-fatigue, and diseases related to the hypothalamus, pituitary, ovary, thyroid or adrenal gland, and malfunction of the HPOA will lead to follicle hypoplasia, delayed follicle maturation, or anovulation [2]. Depending on the pathological mechanisms, the causes of anovulatory infertility can be divided into several categories, including abnormal uterine bleeding-ovulatory disorders (AUB-O), polycystic ovarian syndrome (PCOS), hyperprolactinemia, luteinized unruptured follicle syndrome (LUFS), corpus luteum insufficiency, and premature ovarian insufficiency (POI).

In Western medicine, hormone-induced ovulation and assisted reproduction technology are two main ways to treat anovulatory infertility. The commonly used drugs include clomiphene citrate, letrozole, gonadotropins (Gn), and gonadotropin-releasing hormone (GnRH). ART contains intrauterine insemination (IUI) with or without controlled ovarian hyperstimulation (COH), in vitro fertilization-embryo transfer (IVF-ET), gamete intrafallopian transfer (GIFT), oocyte donation, intracytoplasmic sperm injection (ICSI), preimplantation genetic diagnosis (PGD), etc. [3]. There are several side effects that need to be considered during treatment using modern drugs or techniques. (1) Ovarian hyperstimulation syndrome (OHSS): the overall morbidity of OHSS in ovulation induction is 1–14%. The serious morbidity rate of OHSS is 0.5–2%, including tense ascites, liver and renal function damage, adult respiratory distress (ARDS), and thromboembolism [4]. (2) Complications of puncture and peritoneoscopy when collecting oocytes: these include puncture injury and bleeding, complications of anesthesia, pneumothorax, and mediastinal emphysema in peritoneoscopy and thrombus [5]. (3) Ovulation induction may bring a risk of a high ovulation rate with a low pregnancy rate, high miscarriage rate, multiple pregnancy, and ectopic pregnancy. (4) Ovulation induction surpassing the natural period could elevate the risk of cancer, such as breast cancer, cancer of the genital tract, and melanoma [6–8].

Current clinical trials have shown that traditional Chinese medicine (TCM) was associated with significantly higher pregnancy rates than control treatments, and the ovulation rates between the two groups were not significantly different [9–11]. It is notable that all systemic reviews and meta-analyses have mentioned that there is a lack of high-quality, strong, evidence-based, large-sample randomized controlled trials (RCTs) on this topic.

Bushen Culuan Decoction was created more than 20 years ago. In a previous experimental study evaluating the effectiveness and safety of Bushen Culuan Decoction in treating anovulatory infertility, it was found that Bushen Culuan Decoction had no adverse effect or toxic reaction in acute toxicity tests, reproductive toxicity tests, genetic tests, and teratogenic toxicity tests [12] and significantly promoted follicle maturation, ovulation, and luteinization [13]. A clinical exploratory study showed that Bushen Culuan Decoction significantly increased the pregnancy rate, depressed serum prolactin (PRL), and elevated serum estradiol (E_2_) compared with the control treatment in women with anovulatory infertility [14].

Until now, most studies about TCM treating anovulatory infertility have focused on a single disease in a single center, and there is no study with a large sample size aiming to verify the effectiveness and safety of Bushen Culuan Decoction in treating anovulatory infertility. Based on the results of previous studies, we hypothesized that Bushen Culuan Decoction would improve the pregnancy rate by promoting follicle development and ovulation and improving endometrial receptivity. This study will evaluate that hypothesis.

### Objectives

The objective of this RCT is to evaluate whether Bushen Culuan Decoction enables a higher pregnancy rate than clomiphene citrate in women with anovulatory infertility and to identify the anovulatory diseases for which Bushen Culuan Decoction has higher effectiveness (among AUB-O, PCOS, hyperprolactinemia, LUFS, corpus luteum insufficiency, and POI).

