### Sample size estimation

In a previous study, the total effective rate (Total effective rate% = (markedly effective + effective) / number of patients × 100%) in the experimental group was 90%, and the total effective rate in the control group was 80%. Thus, the difference between the two groups was 10%. We used the calculation formula for superiority trials to calculate the sample size, and the *α* error and *β* error were set at 0.05 and 0.10, respectively. This will require a sample size of 219 participants in each group. The dropout rate is expected to be 20%, which means that a total of 528 patients are needed for the two groups.

This study is an adaptive research study with an interim analysis. In the first stage of the study, 6 hospitals will screen 1/3 of the total sample size, which will be 176 patients. When we calculate the pregnancy rate, the primary outcome of this study, we will go through the first unblinding and interim analysis. The aim of the interim is to find out which of the six diseases are more sensitive to Bushen Culuan Decoction therapy. If Bushen Culuan Decoction shows significant clinical benefit or tends toward a benefit for a certain disease, research on this disease will go into the second stage of the study. If Bushen Culuan Decoction does not reach the treatment effectiveness threshold, research on this disease will be suspended in the next stage. At this time, the sample size will be recalculated according to the interim analysis result.

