#### Statistical analysis

An independent statistician will use SPSS 21.0 (SPSS, Chicago, Illinois, USA) to analyze the data.

The mean ± SD will be used to describe normally distributed data, while medians with IQRs will be used if the data are not normally distributed. The *χ*^2^ test will be used for evaluating differences between dichotomous variables, while one-way analysis of variance or Student’s *t* test will be used for evaluating continuous variables. The Mann-Whitney test will be used if the data are not normally distributed. A *p* value < 0.05 will be considered statistically significant.

If there are dropouts from the study, the last-observation-carried-forward principle will be used to compensate for the loss of data.

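### The first objective covers all six anovulatory diseases, but stage 2 enrols only those kept at the interim; a pooled final comparison would describe an interim-chosen mix, expected to overstate the six-disease effect if effects differ

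*Protocol article*

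**What the plan says.** Objectives (protocol article) sets two aims. The first is to "evaluate whether Bushen Culuan Decoction enables a higher pregnancy rate than clomiphene citrate in women with anovulatory infertility". The second is "to identify the anovulatory diseases for which Bushen Culuan Decoction has higher effectiveness", among six named diseases. The Design section defines the comparison over the same six.

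Sample size estimation fixes one two-group size for that whole population: 219 per group, 528 in total after a dropout allowance. It then makes the trial adaptive. In stage 1, "6 hospitals will screen 1/3 of the total sample size, which will be 176 patients". On timing: "When we calculate the pregnancy rate, the primary outcome of this study, we will go through the first unblinding and interim analysis". A disease showing "significant clinical benefit or tends toward a benefit for a certain disease, research on this disease will go into the second stage of the study". For a disease that "does not reach the treatment effectiveness threshold, research on this disease will be suspended in the next stage". The sample size is then to be recalculated.

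Statistical analysis names one method for binary outcomes: a chi-squared "test will be used for evaluating differences between dichotomous variables", at p < 0.05. The article does not restate the first objective for the diseases kept. Nor does it say how suspended diseases enter the final comparison.

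**The concern.** The population in the first objective and the population that stage 2 supplies are different, and both are fixed in this document. If the total stays at 528, 352 women (two thirds) come only from diseases selected on the very outcome being estimated. A pooled difference then gives each kept disease several times the weight of a suspended one.

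At stake is what the trial may conclude. A headline of a higher pregnancy rate in anovulatory infertility could rest on a sample from which the less favourable diseases had largely been removed. This is separate from the false-positive rate: perfect control of alpha would not make the pooled sample represent all six diseases.

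**Working it through.** **The plan's own figure.** With rates of 90% and 80%, mean rate 0.85, one-sided alpha 0.05 and power 0.90:

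n = 2 × 0.85 × 0.15 × (1.645 + 1.282)² / 0.10² = 218.4, so 219 per group, as stated.

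Inflating by 1.2 gives 263 per group and 526 in total, close to the stated 528. One third of 528 is 176. The concern therefore does not rest on a wrong figure. What matters is that this is a single two-group calculation for the whole population.

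**Inputs for the check.** From the document: six diseases, 1:1 allocation, 176 women in stage 1, total 528, continuation on benefit or a trend. Assumed, because the document does not give them:
- an even disease mix, with 15 and 14 women per arm in each disease at the interim;
- a 20% control pregnancy rate (the 80% and 90% figures are a total effective rate);
- continuation if the observed difference is above 0;
- 528 − 176 = 352 stage-2 women, shared equally among the kept diseases.

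**Hand check of the weights.** If three diseases are kept, each has 29 + 352/3 ≈ 146 women, against 29 in a suspended disease. The kept three make up 3 × 146.3 / (174 + 352) = 0.83 of the sample. If the true effect is +20 points in exactly those three and 0 in the others, the enrolled-mix effect is 0.83 × 20 = 16.7 points, against a six-disease average of 10.0.

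**Simulation over the interim's chance outcomes** (40,000 runs per scenario; percentage points):

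| True effects by disease | Six-disease average | Pooled, all women kept | Excess |
|---|---|---|---|
| +10 in all six | 10.0 | 10.0 | 0 |
| +15 in three, +5 in three | 10.0 | 10.6 | 0.6 |
| +20 in three, 0 in three | 10.0 | 12.5 | 2.5 |
| +30, +15, 0, 0, −5, −10 | 5.0 | 10.6 | 5.6 |

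In the third scenario the 5th to 95th percentile of the enrolled-mix effect is 10.0 to 16.7. A continuation threshold of +5 points gives nearly the same excesses. A separate set of runs, with other effect patterns and control rates from 20% to 80%, gave excesses of about 1.5 to 6.5 points when effects differ.

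**If suspended diseases are left out.** With +10 in all six, the estimate for the kept diseases averages about 12.1 against a true 10.0. With no effect anywhere it averages about 2.4 against 0. The kept diseases' favourable stage-1 error stays in the estimate, so it is biased upward by about 2 points even with equal effects.

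**A repair that fails.** Suppose each disease's difference is combined with fixed equal weights, using stage 1 only for suspended diseases and both stages for kept ones. In a suspended disease the low stage-1 error is frozen. In a kept disease the high stage-1 error is diluted by stage 2. The two no longer cancel:

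| True effects | Truth | Weighted estimate |
|---|---|---|
| +20 in three, 0 in three | 10.0 | 6.5 |
| +10 in all six | 10.0 | 5.9 |
| 0 in all six | 0 | −4.7 |
| +30, +15, 0, 0, −5, −10 | 5.0 | 1.6 |

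**A repair that works.** An estimate from the stage-1 women alone, taken before selection, is unbiased in all of these scenarios. Its standard error at a 25% rate is √(0.25 × 0.75 × 2/88) = 6.5 points.

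**The case against.** Three points have force.

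First, a reader might infer that the pooled difference always overstates the effect. The documents do not support that. With equal effects and all stage-1 women kept there is no bias, and with mild heterogeneity the excess is under one point. In a single trial the drift can also go down (about 3 to 5% of runs in the two strongly heterogeneous scenarios). What makes heterogeneity the natural premise is the plan itself: the second objective and the interim both look for diseases that respond better.

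Second, a reader might infer that the plan commits to a pooled final test. It does not say so. Pooling is implied by one two-group sample size and one unstratified test. The keyword describing a basket design and the second objective are compatible with disease-level reporting, and how the stages are combined is detail that a condensed article may leave to the full plan. This makes the bias conditional. It does not remove the mismatch, since the objective and the suspension rule both stand in this document and describe different populations.

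Third, recruitment is fixed per hospital (88 each), not per disease, so even the stage-1 mix is simply what six hospitals enrol. The stage-2 size is to be recalculated, so 352 and two thirds are assumptions. Both limit the precision of the figures, not the argument.

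**Conclusion.** The point holds in conditional form. The first objective is worded for all six diseases, while stage 2 is restricted to diseases selected on the unblinded primary outcome, so a pooled final comparison would not answer the objective as written. Under the stated assumptions the expected excess over the six-disease effect runs from nil (equal effects, all stage-1 women kept) through 0.6 points (mild heterogeneity) to 2.5 and 5.6 points (strong heterogeneity). The sample size rests on a 10-point difference, so the upper part of that range matters. The true size cannot be settled from the document, because it gives no continuation threshold, disease mix, control pregnancy rate or pooling rule. It should be corrected, but it does not by itself invalidate the design.

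**What to change.** In Objectives and Sample size estimation:

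1. Word the confirmatory claim only for the named diseases retained at the interim, using inference that allows for the selection: for example stage-2 data alone, or a stage-wise combination test.
2. Do not report the pooled final sample as representing women with anovulatory infertility in general.
3. If a six-disease answer is wanted, estimate it from the stage-1 women only, in all six diseases and before selection, and label it exploratory.
4. Do not combine stage-1 data of suspended diseases with two-stage data of retained diseases under fixed weights unless selection is corrected for. Uncorrected, that estimate was about 3.4 to 4.7 points too low in the scenarios above.

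The cost is mostly wording. Relying on stage-2 data alone gives up the stage-1 information on the retained diseases; a stage-wise combination recovers it. The six-disease estimate is imprecise: a standard error of 6.5 points means a 95% interval of roughly ±13 points (1.96 × 6.5).

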## Methods

### Design

This is a randomized, double-blinded, double-dummy, parallel, positively controlled, adaptive, multicenter clinical trial comparing the pregnancy rate after treatment with Bushen Culuan Decoction versus treatment with clomiphene citrate in women suffering from anovulatory infertility caused by AUB-O, PCOS, hyperprolactinemia, LUFS, corpus luteum insufficiency, or POI, and the flow chart and assessment timepoints are shown in Figs. 1 and 2. The study protocol will be drafted in accordance with the guidelines of the Standard Protocol Items: Recommendations for Interventional Trials (SPIRIT). This study has been registered at www.clinicaltrail.gov (NCT03709849).

**Fig. 1 Fig1:**
[figure not shown]
Study flow chart. AMH: anti-Mullerian hormone; INHB: inhibin B; PI: pulsatility index

**Fig. 2 Fig2:**
[figure not shown]
Traditional Chinese Medicine symptom score

### Patient and public involvement

At the stage of research scheme formulation, the research group invited patients to participate in the scheme feasibility review meeting, and the researchers fully listened to and adopted the opinions of patients, especially in determining the return visit time and drafting informed consent. The final report of the patient’s study will also be fed back to the patient.

### Ethics approval

This study has been approved by the Medical Ethics Committee of Xiyuan Hospital China Academy of Chinese Medical Sciences (No. 2017XLA037-2). Ethical amendment approval will be required if the protocol needs to be modified. All patients are required to sign an informed consent form before joining the study. Clinical investigators must make sure that the participant knows very well the whole process of the study and the benefits and risks she will be subject to whether she is in the experimental group or the control group.

### Sample size estimation

In a previous study, the total effective rate (Total effective rate% = (markedly effective + effective) / number of patients × 100%) in the experimental group was 90%, and the total effective rate in the control group was 80%. Thus, the difference between the two groups was 10%. We used the calculation formula for superiority trials to calculate the sample size, and the *α* error and *β* error were set at 0.05 and 0.10, respectively. This will require a sample size of 219 participants in each group. The dropout rate is expected to be 20%, which means that a total of 528 patients are needed for the two groups.

This study is an adaptive research study with an interim analysis. In the first stage of the study, 6 hospitals will screen 1/3 of the total sample size, which will be 176 patients. When we calculate the pregnancy rate, the primary outcome of this study, we will go through the first unblinding and interim analysis. The aim of the interim is to find out which of the six diseases are more sensitive to Bushen Culuan Decoction therapy. If Bushen Culuan Decoction shows significant clinical benefit or tends toward a benefit for a certain disease, research on this disease will go into the second stage of the study. If Bushen Culuan Decoction does not reach the treatment effectiveness threshold, research on this disease will be suspended in the next stage. At this time, the sample size will be recalculated according to the interim analysis result.

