### Outcome measures

#### Primary outcome

The primary outcome is pregnancy rate (confirmed by serum β-HCG positivity).

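### The sample size is calculated for a total effective rate that is not an outcome of this trial, so 90% power is not established for the primary outcome, pregnancy rate

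*Protocol article*

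**What the plan says.** All the planning inputs are in the protocol article, Methods, Sample size estimation. The endpoint is defined as "Total effective rate% = (markedly effective + effective) / number of patients × 100" per cent. The rate in a previous study "in the experimental group was 90%, and the total effective rate in the control group was 80" per cent, and "Thus, the difference between the two groups was 10" percentage points. The method is described as follows: "We used the calculation formula for superiority trials to calculate the sample size". The α and β "error were set at 0.05 and 0.10, respectively". The result is: "This will require a sample size of 219 participants in each group". With 20% dropout the total is given as 528.

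The Primary outcome section reads: "The primary outcome is pregnancy rate (confirmed by serum β-HCG positivity"). The Sample size estimation section agrees, because its account of the interim says: "When we calculate the pregnancy rate, the primary outcome of this study, we will go through the first unblinding and interim analysis". The Objectives and Design sections are also framed on pregnancy rate.

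The Secondary outcomes list covers ovulation rate, temperature, hormones, ultrasound measures, coagulation and the symptom score. Total effective rate is not in it, and its two response grades are not defined anywhere in the article. No pregnancy rate is assumed for either group. The sample size is to be recalculated after the interim, with no target or rule given.

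**The concern.** A power statement holds for one endpoint, one pair of rates and one test. Here the rates belong to a graded response that the trial does not list, while the efficacy conclusion and the interim decisions on the six diseases rest on pregnancy.

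The difference is more than a label. For a fixed absolute difference, the variance of a proportion is smaller near 80–90% than in the middle of the range. A size computed at 80–90% carries over to pregnancy only if pregnancy rates lie at a similar distance from 0 or 100%. Otherwise a true 10-point gain is missed more often than the stated 10% of the time. The planning total also sets the first stage of 176 patients (one third of 528), after which diseases continue or are suspended.

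**Working it through.** **Inputs from the article.** Rates 0.90 and 0.80, difference d = 0.10, α = 0.05, power 0.90, allocation 1:1, 219 per group, 528 in total (264 per group). The Statistical analysis section plans a χ² test with p < 0.05. Sidedness of the sample size calculation is not stated.

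**Step 1: reproduce 219.** Use n = 2·p̄(1−p̄)·(z_α + z_β)² / d², with p̄ = 0.85 and z_β = 1.2816.

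- One-sided α 0.05 (z = 1.6449): 2 × 0.85 × 0.15 × (1.6449 + 1.2816)² / 0.01 = 218.4, so 219. This is an exact match.
- Two-sided α 0.05 (z = 1.9600), same formula: 267.9, so 268. Other two-sided variants give 263 (unpooled), 266 (pooled null variance only) and 286 (with continuity correction).

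The 219 therefore belongs to 90% vs 80% and to a one-sided 5% test. With a two-sided test, 219 per group gives 84% power even at 90% vs 80%.

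**Step 2: power for pregnancy rate.** The article gives no pregnancy rate and no target difference. *Assumptions:* control rates of 10% to 40% and the same 10-point difference.

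Power = Φ{ [d√n − z_α√(2p̄(1−p̄))] / √(p₁(1−p₁) + p₂(1−p₂)) }.

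Example, 30% vs 40%, n = 219: d√n = 1.480, √(2 × 0.35 × 0.65) = 0.6745, √(0.21 + 0.24) = 0.6708.

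- One-sided: (1.480 − 1.6449 × 0.6745) / 0.6708 = 0.552, power 71%.
- Two-sided: (1.480 − 1.9600 × 0.6745) / 0.6708 = 0.235, power 59%.

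| Control vs experimental | One-sided, 219 per group | Two-sided, 219 per group | Two-sided, 264 per group | n per group for 90% power, one-sided / two-sided |
|---|---|---|---|---|
| 10% vs 20% | 90% | 84% | 90% | 217 / 266 |
| 20% vs 30% | 78% | 68% | 76% | 320 / 392 |
| 30% vs 40% | 71% | 59% | 67% | 388 / 477 |
| 40% vs 50% | 68% | 56% | 64% | 423 / 519 |

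The one-sided column keeps the test that produced 219 and changes only the rates, so it isolates the endpoint mismatch. The step to the two-sided column is sidedness. The 10% vs 20% row is the mirror image of 90% vs 80% and so has the same power.

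**Step 3: detectable difference.** With 219 per group and 90% power, for control rates of 20% to 40%, the detectable difference is 12.2 to 13.9 points one-sided, or 13.7 to 15.4 points two-sided.

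**The case against.** **The shortfall is conjecture.** With no pregnancy rate in the article, nobody can say that power is low, and at 10% vs 20% the one-sided power is the planned 90%. This stands as a limit on magnitude: the figures are a conditional range. It does not touch the main point, which needs no assumed rate. A reader might infer that pregnancy rates of 80–90% are out of the question and that the trial is therefore certainly underpowered. The article gives no rate from which to judge that, and the 10-point target for pregnancy is itself an assumption.

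**The fall to 56–68% is not all due to the endpoint.** Correct. A reader might attribute the whole drop from 90% to the mismatch, but on the one-sided basis behind 219 the figures at control rates of 20%, 30% and 40% are 78%, 71% and 68%. The lower figures remain relevant, because a χ² test at p < 0.05 is ordinarily two-sided.

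**More than 219 per group may be analysed.** Also fair. The plan enrols 264 per group and carries the last observation forward for dropouts. Two-sided power is then 90%, 76%, 67% and 64% for the four rows. These are upper bounds, because counting dropouts as not pregnant would dilute the difference.

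**The interim recalculation deals with it.** In part. It makes 528 provisional, so it does not follow that a null result would rest on 528 patients. But no target difference or rule is stated, and a later recalculation does not turn 219 into a calculation for pregnancy.

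**Pregnancy may have counted towards an effective response in the previous study.** The article does not say so, and two response grades combined would still not be the pregnancy rate.

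**Conclusion.** The mismatch is established from the article's own text: the size and the β of 0.10 rest on an endpoint that this trial does not list, and 90% power is not established for the primary test. This holds whatever the pregnancy rate turns out to be.

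The consequence is conditional. If the gain of interest is 10 points and the control pregnancy rate is 20–40%, a true gain would be missed with probability 22–32% on the one-sided basis behind 219, or 32–44% with a two-sided test, against the stated 10%. If the control rate is near 10%, the mismatch costs nothing and only the sidedness loss remains (90% to 84%). The documents do not support a single power figure or a claim that the trial is definitely underpowered. The planned recalculation mitigates the problem without curing it.

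**What to change.** In Sample size estimation:

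- Keep the historical basis visible: say that 219 and 528 came from the total effective rate of the previous study.
- State the assumed control pregnancy rate, the target difference and the sidedness of the primary test.
- Restate either the power that the planned size gives for pregnancy rate or the difference detectable with 90% power.

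If the interim recalculation has not yet been done, base it on pregnancy rate with a prespecified minimum relevant difference. The Trial status section expected recruitment to finish around February 2022 and the article appeared in July 2022, so this step may already have passed. In that case the disclosure and the restated power are what remains.

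The cost is a wording amendment and, unless the control rate is near 10%, a less favourable stated power. If the recalculation is still open and 90% power is to be kept for a 10-point gain, the table shows that more patients would be needed at control rates of 20% or above.

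### At the stated β of 0.10, 219 per group follows only from a one-sided 5% formula, but the planned χ² test at p < 0.05 is non-directional; on that basis power is about 84%, not 90%

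*Protocol article*

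**What the plan says.** The Sample size estimation section of the protocol article takes its rates from a previous study: the total effective rate "in the experimental group was 90%, and the total effective rate in the control group was 80" per cent. The α and β "error were set at 0.05 and 0.10, respectively". On method it says only "We used the calculation formula for superiority trials to calculate the sample size", without giving the sidedness, and it concludes "This will require a sample size of 219 participants in each group". Adding an expected 20% dropout, it arrives at 528 women in total, which is 264 per group at 1:1 allocation.

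The Statistical analysis section names the χ² test and says this "test will be used for evaluating differences between dichotomous variables", with the rule that a p "value < 0.05 will be considered statistically significant". The Abstract repeats the threshold. Neither place mentions a one-sided test.

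**The concern.** A sample size, its error rates and the planned test should describe one procedure. The Pearson χ² test on a 2×2 table squares the difference, so at p < 0.05 it is the two-sided z test with critical value 1.960. A one-sided 5% calculation uses 1.645. If the number was derived with 1.645 and the result will be judged at 1.960, the stated β of 0.10 is not delivered.

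Two things are at stake. The first is the chance of missing the assumed effect. The second is the rule for claiming success: at one-sided 5% the nominal chance of wrongly declaring the decoction better is 5%, while under a two-sided 5% test it is 2.5% in that direction. The section also says the sample size will be recalculated after the interim analysis, so an undeclared convention could carry into the second stage.

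**Working it through.** **Inputs.** p₁ = 0.90, p₂ = 0.80, difference 0.10, α = 0.05, β = 0.10, n = 219 per group, 20% dropout, total 528 (all from Sample size estimation); 1:1 allocation (Abstract); χ² test at p < 0.05 (Statistical analysis). Normal quantiles: 1.645 (one-sided 5%), 1.960 (two-sided 5%), 1.282 (90% power). The mean rate is p̄ = 0.85, so 2p̄q̄ = 2 × 0.85 × 0.15 = 0.255. The unpooled variance is 0.90 × 0.10 + 0.80 × 0.20 = 0.25.

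**Step 1: reproduce 219.** Average-proportion formula, n = (z_α + z_β)² × 2p̄q̄ / d²:

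- One-sided 5%: (1.645 + 1.282)² × 0.255 / 0.01 = 8.564 × 25.5 = 218.4, so 219. This is the article's figure.
- Two-sided 5%: (1.960 + 1.282)² × 0.255 / 0.01 = 10.507 × 25.5 = 267.9, so 268.

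**Step 2: check that another formula does not explain it.** Per-group n at β = 0.10:

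| Formula | One-sided 5% | Two-sided 5% |
|---|---|---|
| Arcsine | 213 | 261 |
| Unpooled variance | 215 | 263 |
| Pooled variance under the null | 217 | 266 |
| Average proportion | 219 | 268 |
| Pooled with continuity correction | 237 | 286 |

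No two-sided entry is below 261. Outside the stated β there is one other route: two-sided 5% with 80% power and a continuity correction gives 218.5, also 219. That would need β = 0.20.

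**Step 3: power of the planned test.** With the pooled null variance, power = Φ[(d√n − 1.960√0.255) / √0.25], and 1.960 × √0.255 = 0.990.

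- n = 219: (1.480 − 0.990) / 0.5 = 0.980, so 83.7%. Exact enumeration of the Pearson χ² test gives 84.4%.
- n = 211 (528 × 0.80 / 2 = 211.2): (1.453 − 0.990) / 0.5 = 0.926, so 82.3% (exact 82.9%).
- n = 264 (nobody lost): (1.625 − 0.990) / 0.5 = 1.270, so 89.8% (exact 90.4%).

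For comparison, one-sided 5% at 219 gives 90.3% (exact 90.9%), in line with the stated β.

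**Step 4: size.** At 219 the type II error is 1 − 0.837 = 0.163, about 1.6 times the stated 0.10. The shortfall is 90 − 83.7 = 6.3 points at 219 and 90 − 82.3 = 7.7 points at 211. The two-sided requirement of 266 is 266 / 219 = 1.21 times the stated number.

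**The case against.** The strongest defence is that 219 is no miscalculation: it follows correctly from the stated inputs under a one-sided superiority formula, and the trial's objective is directional. The analysis sentence is also generic, covering every dichotomous variable, and a fuller document might declare the sidedness. It stands that the arithmetic is sound for a one-sided test and that the mismatch is inferred, since the article never states sidedness for the calculation or the test. It does not remove the point: the article itself prints α, β, the number and a non-directional test, and these do not fit together.

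The second defence concerns dropouts. Statistical analysis carries the last observation forward, and Withdrawal criteria treats a withdrawn woman's last results as final, so up to 264 per group could be analysed. Power would then be 89.8%, provided the assumed rates also hold in the dropouts. This too stands, as a conditional statement. But the sizing treats the women above 219 as an allowance for loss, and if the 20% lost all counted as failures, the difference would shrink to 0.8 × 0.90 − 0.8 × 0.80 = 0.08.

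Three stronger readings are tempting and not supported:

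- That 219 can arise only from a one-sided test. This is true only at β = 0.10, because the two-sided, continuity-corrected calculation at 80% power gives the same number.
- That the shortfall reaches about 12 points. This needs a continuity correction (80.1% at 219, 78.5% at 211), which the article does not mention.
- That the trial's power simply is 84%. That figure belongs to 219 analysed per group and to the total effective rate, whereas the primary outcome is the pregnancy rate.

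**Conclusion.** The point holds as a mismatch between the sample size and the planned test. The stated rates, error rates, 219 per group and a χ² test at p < 0.05 cannot all be true together. On the article's own sizing basis, two-sided power is about 84% at 219 evaluable per group and about 82% at 211, which is 6 to 8 points below the stated 90%.

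This rests on four assumptions: the 90% and 80% rates as given, the χ² test read in its usual non-directional sense without continuity correction, 1:1 allocation, and dropouts counted as lost, as the sizing does. If all 264 per group were analysed at the assumed rates, the gap would almost vanish. The figures describe the total effective rate, say nothing about power for pregnancy, and lapse if those inputs are replaced.

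**What to change.** In Sample size estimation, state whether the calculation is one- or two-sided and make it agree with Statistical analysis.

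- If two-sided: restate the power as about 84% at 219 evaluable per group (about 82% at 211), and note that 90% would need about 266 evaluable per group.
- If one-sided 5% is intended: say so in Statistical analysis for the primary comparison, with the decision rule that applies.

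Use the same sidedness in the sample-size recalculation after the interim analysis. If pregnancy rates replace the total effective rate as inputs, redo all of these figures.

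Either route costs about a sentence per section; the two-sided one also means a less favourable stated power. Raising the evaluable number to 266 is a much larger change, and this correction does not require it.
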